### Concealment mechanism {16b}

The independent statistician was provided with a file containing only the diabetes centre identification codes and stratification variables and no identifying information.

## Assignment of interventions: blinding

### Who will be blinded {17a}

The project lead and primary investigator will not be blinded to group allocation as they will be delivering the interventions, but they will only be aware of the site practice and outcome data pertaining to any given diabetes centre in a coded manner, as each participating diabetes centre has a unique identifying code. The ANDA Secretariat is the only person who has access to the codes linking diabetes centre IDs with their contact details and is not involved in the delivery of the intervention, assessment of outcome or analysis.

Other investigators and the biostatistician supervising the analysis will be blinded to group allocation. The data analysis team will be blinded to allocation details for the purpose of data analysis.

Participating diabetes centres will be blind to group allocation until the delivery of the interventions. Due to the nature of the intervention and control in this study, it will not be possible to blind the participating sites to the intervention they receive.

### Procedure for unblinding if needed {17b}

As this is a cluster randomised trial, sites (the participating diabetes centres) are not blinded due to the nature of the intervention.

## Data management

### Plans to promote participant retention and complete follow-up {18b}

Participating sites have the right to withdraw from the study at any time, with no consequences for withdrawal. Sites who do not participate or who withdraw from this trial (but not from ANDA) will receive the augmented ANDA feedback reports and full data appendix, as per standard processes. We have allowed for site withdrawals in the sample size calculations. If any site decides not to subsequently receive the intervention and withdraws, the de-identified (coded) clinical outcome data from the patients of this site will still be collected for this trial as part of the routine ANDA data collection that the sites have agreed to participate in.

### Data management {19} and confidentiality {27}

All data will be downloaded and electronically stored in line with applicable privacy principles. As part of ANDA data management, data collected with the standardised data collection form is checked by the data management team, with queries sent to participating diabetes centres regarding any data anomalies (such as out-of-range data). Once the data queries have been resolved, the ANDA dataset is checked by an independent data specialist [13].

All data will be password protected and will be housed on a secure Monash University Server, as per standard ANDA protocol [8]. The chief investigator, data manager and project lead will be the only researchers to have access to the data. All researchers on this project are involved in projects using research databases which have high levels of security. This electronic database will remain in password-secured storage for 7 years and then deleted from all backups.

### Plans for collection, laboratory evaluation and storage of biological specimens for genetic or molecular analysis in this trial/future use {33}

No biological specimens are being collected as part of this trial.

## Statistical methods

### Statistical methods for primary and secondary outcomes {20a}

#### Primary outcomes

Differences between the experimental and control groups will be analysed by the intention-to-treat approach. For the first co-primary outcome of difference in HbA1c, we will use the linear mixed effects model to compare the between-group difference in mean HbA1c at 6 months after delivery of the intervention while adjusting for clustering of patients with site by including a centre random intercept. Appropriate transformations of the data will be undertaken in the event of departure from normality. Only if the first co-primary outcome is statistically significant at a two-sided level of significance of <0.05, we will test the second co-primary of acceptability and utility of interventions for superiority using the chi-squared or Fisher’s exact test as appropriate. This will preserve the overall type 1 error at <0.05.

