### Eligibility criteria {10}

#### Inclusion criteria

##### Diabetes centres

Australian diabetes centres (Centres of Excellence, primary, secondary and tertiary care services) registered with the National Association of Diabetes Centres (NADC) will be eligible for inclusion in the trial if the following criteria are met: (i) at least one representative of the practice (the designated contact person for ANDA) provides written informed consent; (ii) the practice participates in ANDA in 2021 (irrespective of whether they have or have not participated in previous years). Differences between types of eligible diabetes centres are shown in Table 1.

**Table 1 Tab1:** Differences between types of eligible diabetes centres (based on the criteria set out by the NADC)

Type of centre	Definition
Primary care centres	General practices or community health centres that work closely with the local general practitioners to provide care for people with diabetes
Secondary care centres	Services with a range of full and/or part-time diabetes staff but who often do not have an endocrinologist as part of their usual team
Tertiary care centres	Diabetes centres that have the full range of diabetes service providers including endocrinologists, diabetes nurse educators, psychologists, dietitians and podiatrists on staff (full time) and have been accredited by the NADC
Centres of Excellence	Recognised diabetes centres that have demonstrated excellence in education, research, service delivery, practice/policy development and education. These centres must be tertiary-level facilities

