##### Acceptability and utility of the intervention at 3 months

To assess how well the interventions address the issues raised in our formative work [16] at a practitioner level, the acceptability and utility of the intervention will be assessed via a 15-min online survey, which we will design specifically for this purpose. This survey will adapt on a survey (ENACT) used by a group of audit and feedback researchers with permission from the authors (personal communication) to assess the acceptability of online audit and feedback interventions [20]. The ENACT survey will be adapted to allow inclusion of parts of an existing ANDA questionnaire. Surveys will be completed 3 months after the delivery of site reports (feedback). Participants will rate a variety of factors about the feedback using Likert scales and open-ended text comments. The developed, combined survey will be validated for test/retest reliability and face validity prior to its use in outcome assessment (see sub-study below). The survey will be delivered to participants as an email link sent to the registered contact persons for the participating sites and will be conducted through REDCap [21], a secure web application for online survey and database management hosted at Monash University. The survey will be delivered 3 months after the delivery of the ANDA feedback reports.

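### The second co-primary consists of ordered Likert ratings but is tested with chi-squared or Fisher's exact, which costs power and makes no provision for a centre with more than one respondent

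*Protocol article*

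**What the plan says.** The protocol article, Statistical methods {20a}, Primary outcomes, fixes the test for the second co-primary: "we will test the second co-primary of acceptability and utility of interventions for superiority using the chi-squared" or Fisher's exact test, whichever is appropriate. The same paragraph handles HbA1c by "adjusting for clustering of patients with site by including a centre random intercept"; no centre term is given for the survey outcome. The survey is reached through a gate, "Only if the first co-primary outcome is statistically significant at a two-sided level of significance of <0.05", and the paragraph concludes "This will preserve the overall type 1 error at <0.05".

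The section on acceptability and utility at 3 months describes the data: "Participants will rate a variety of factors about the feedback using Likert scales and open-ended text comments". The Background of the survey sub-study adds that there will be an overall rating as well as section-by-section questions.

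On who answers, the eligibility section requires that "at least one representative of the practice (the designated contact person for ANDA) provides written informed consent". The survey goes out as "an email link sent to the registered contact persons for the participating sites". The Feedback report section speaks of a single contact person for each centre. The abstract places the outcome at practitioner level, while the centre is the unit of randomisation.

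**The concern.** The hypothesis is directional: the co-intervention should move ratings upwards. A chi-squared test over all response levels spends its degrees of freedom on any difference in pattern, and a two-by-two test discards the grading within each half. Either way a consistent upward shift is harder to detect. That matters with about 70 respondents, in a trial whose sample size rests on HbA1c alone.

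Independence is a separate, conditional matter. If some centres return several surveys, responses within a centre are likely to be correlated. A test that treats them as independent then gives p-values that are too small, and the stated protection of the 0.05 level would rest on an assumption that the text does not secure.

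**Working it through.** **The plan's own figure.** The protocol gives no power for the survey, only for HbA1c, which opens the gate. Inputs from Sample size {14}: difference 0.5, SD 2.3, ICC 0.070, CV of cluster size 0.730, 35 sites per arm, 3500 patients (3500/70 = 50 per site).
- λ = 50×0.07/(50×0.07 + 0.93) = 0.790
- Relative efficiency = 1 − 0.73²×0.790×0.210 = 0.912
- Design effect = (1 + 49×0.07)/0.912 = 4.86
- Effective n per arm = 1750/4.86 = 360
- Power = 83.1% (normal) or 82.0% (t, 68 df)

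This agrees with the stated figure of at least 80% and is unaffected by the point made here.

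**Power for the survey.** Assumptions, none of them in the protocol: a five-level item; control distribution 5/15/30/35/15%; a proportional-odds shift (cumulative odds divided by the odds ratio); 35 respondents per arm, one per centre; two-sided 0.05. Each setting was simulated 5,000 times, so the standard error is at most √(0.25/5000) = 0.7 points.

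| Odds ratio | Wilcoxon | Chi-squared, top two | Fisher, top two | Chi-squared, five levels | Shortfall against Wilcoxon (points, same order) |
|---|---|---|---|---|---|
| 2 | 34.4% | 26.7% | 19.9% | 18.9% | 8, 15, 16 |
| 2.5 | 53.9% | 44.6% | 36.4% | 32.3% | 9, 18, 22 |
| 3 | 70.1% | 58.3% | 48.9% | 45.3% | 12, 21, 25 |

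A second run at odds ratio 3 gave 70%, 59%, 50% and 46%, that is, shortfalls of 11, 20 and 24. Allowing for simulation error, the losses over odds ratios 2 to 3 are about 8 to 11, 15 to 20 and 16 to 24 points.

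**Type I error, one response per centre.** With no true difference the rejection rates were 4.3% (five-level chi-squared), 4.0% (top-two chi-squared) and 2.2% (Fisher). There is no inflation.

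**Type I error, r responses per centre.** The size of an unadjusted test is 2×[1 − Φ(1.96/√(1 + (r − 1)×ICC))], with an assumed ICC of 0.05 to 0.30.
- r = 2: design effect 1.05 to 1.30, size 5.6% to 8.6%
- r = 3: design effect 1.10 to 1.60, size 6.2% to 12.1%

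**Effect of the gate.** If HbA1c truly differs and the survey outcome does not, the overall error is the chance that the gate opens and the survey test rejects. It approaches the size of the survey test as HbA1c power approaches 1. At 83% power, and treating the two tests as independent, it is 0.83×5.6% = 4.6% at the low end and 0.83×12.1% = 10.0% at the high end. The gate therefore dampens an inflated second test but does not repair it.

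**The case against.** The strongest reply has four parts.

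*One respondent per centre is the natural reading.* The eligibility text identifies the representative as the contact person, the feedback report goes to a single contact, and the plural in the survey section is most simply a plural across sites. A reader might infer that the planned test ignores clustering and inflates the error rate. The documents do not support that as a flat statement: with one response per centre there is nothing to adjust for. What remains is that the eligibility wording sets a minimum and no maximum, the consent section speaks of individual staff taking part, and no fallback is planned.

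*A top-two chi-squared test is valid and readable.* At odds ratio 3 its expected counts are about 22 and 13 per arm, so choosing the test as appropriate would give chi-squared and not Fisher. The five-level table has expected counts of about 1.2 and 3.7 in its lowest levels, where plain chi-squared would hardly be chosen. A reader might also infer that cutting the scale in two discards most of the information. It does not. Under proportional odds, the efficiency of the top-two split relative to the rank test for the assumed control distribution is (1 − 2×0.5³)/(1 − 0.05³ − 2×0.15³ − 0.30³ − 0.35³) = 0.750/0.923 = 0.81. About a fifth is lost. This stands, and the smallest loss in the table is the fairest for a dichotomised rating.

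*The outcome is tested only after HbA1c succeeds, and no target effect is stated.* This is true. It cannot be said that the choice of test decides whether the co-primary is shown.

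*An analysis plan may define the score or the cut-point.* It may, and their absence from the article is not criticised here. The protocol nevertheless fixes the family of tests, and a plan that follows it inherits the mismatch.

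**Conclusion.** The point holds as a matter of efficiency. The protocol names tests that do not use the ordering of ordered data, and a standard alternative was more powerful at every odds ratio tried. The loss is about 8 to 11 points at best (top-two chi-squared) and up to about 24 points at worst (unordered five-level chi-squared). These sizes depend on the assumed response distribution, a proportional-odds shift and about 35 responses per arm.

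The error-rate part is conditional. On the likelier reading, one respondent per centre, the 0.05 level is kept. If centres return two or three responses, the true size of the survey test is about 6 to 12% for an assumed ICC of 0.05 to 0.30, and the unqualified claim about overall error is not secured. At the planned HbA1c power it could still hold at the low end of that range. The power figures and the inflated sizes belong to different scenarios and should not be added together. The test should be changed before the survey is analysed, but the planned analysis is not invalid as it stands.

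**What to change.** - State how many people per centre answer the survey.
- Name the overall acceptability and utility rating as the quantity tested. If these are two separate ratings, say which one carries the test.
- With exactly one response per centre, use a Wilcoxon test stratified by the randomisation strata (centre type and location). Alternatively, fit a proportional-odds model with arm and strata.
- If any centre gives more than one response, use the proportional-odds model and add a centre random intercept or cluster-robust standard errors.
- Report the difference in the top-two proportion descriptively, so that a readable figure is kept.
- Attach a coded study centre identifier and stratum to each response. The consent section keeps the centre's ANDA number from the project lead, and the blinding section keeps the Secretariat out of outcome assessment. A separate study code, issued by the Secretariat without sight of the responses, would respect both.

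The cost is revised analysis wording and minor survey set-up work. The code has to be in place before the links are sent. The main effect becomes an odds ratio or rank measure rather than a difference in proportions.

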#### Secondary outcomes

Other secondary clinical endpoints (e.g. mean LDL-Ch) and exploratory outcomes (e.g. mean HbA1c at 18 months) will similarly be analysed using the linear mixed effects model.

### Interim analyses {21b}

No interim analyses are planned in this trial.

### Methods for additional analyses (e.g. subgroup analyses) {20b}

Additional subgroup analyses are not planned in this trial.

### Methods in analysis to handle protocol non-adherence and any statistical methods to handle missing data {20c}

The primary analysis is per intention to treat, i.e. any sites that are non-adherent to the intervention will be analysed accordingly to the intervention arm assigned during randomisation. Data analysis will be based on complete cases and there will be no imputation for missing data.

In order to understand the engagement with the interventions, a per-protocol sensitivity analysis will also be completed to assess the fidelity adherence to the intervention and components therein. This will be evaluated in two ways. Firstly, we will include self-report items in the acceptability and utility survey related to the use of each component of the intervention (e.g. Did you access the webinar?). This data will be triangulated with web analytics from the NADC website to show the proportion of participants who access each component of the cointerventions and the time that participants report spending on these components.

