### Strategies to improve adherence to interventions {11c}

The trial will be promoted by the clinical partners (NADC) to their members who have participated in ANDA in 2021. A potential limitation of the recruitment strategy is that this is a pragmatic trial utilising an existing audit and feedback activity, where participation in ANDA 2021 has been impacted by the effects of COVID-19 on clinical practice [18]. As such, there is a lower than usual number of eligible diabetes centres from which to recruit, and the ANDA-EFFECT investigator group acknowledge that it may be difficult to reach optimal sample size; however, all efforts will be made to maximise participation.

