##### HbA1c at 6 months

HbA1c is routinely collected for patients from participating diabetes centres as part of ANDA. Baseline de-identified (coded) mean HbA1c percentage will be extracted for each participating diabetes centre from routine ANDA data collection in 2021. Follow-up data will be collected as part of the ANDA 2022 audit (6 months after delivery of the 2021 ANDA site reports).

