## Assignment of interventions: allocation

### Sequence generation {16a} and implementation {16c}

The random allocation sequence was generated by a senior biostatistician independent to the study in order to allocate the participating diabetes centres (clusters) into the experimental group (enhanced feedback and cointervention) and the control group (enhanced feedback) using random block sizes 2 and 4, stratified by type of centre (primary/secondary care vs tertiary care or Centres of Excellence (CoE)) and location (metropolitan or rural), based on centres who participated in ANDA 2019. Due to the low numbers of Centres of Excellences and the similarity to tertiary care centres, these types of centres will be combined for the purpose of stratification and analysis. We based the randomisation on 2019 ANDA participation and randomised prior to the formative qualitative work [16] to avoid potential contamination of the trial control group. As such, randomisation occurred prior to commencement. In addition, any centres who participated in ANDA for the first time in 2021 were allocated to either the intervention or the control arm as per the outlined randomisation method. Participants will be enrolled by the project lead as per section {26a}.

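### Complete cases are fixed and the HbA1c model has no baseline term, so each enrolled centre's 2021 mean, already extracted, protects neither precision nor against differential loss of centres

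*Protocol article*

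**What the plan says.** **Missing data.** Section {20c} states for all outcomes: "Data analysis will be based on complete cases and there will be no imputation for missing data". The same section promises one sensitivity analysis: "a per-protocol sensitivity analysis will also be completed to assess the fidelity adherence to the intervention and components therein". That concerns engagement, not missing data.

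**HbA1c model.** Under Statistical methods, Primary outcomes, a linear mixed model with a centre random intercept is used "to compare the between-group difference in mean HbA1c at 6 months after delivery of the intervention while adjusting for clustering of patients with site". Neither a 2021 HbA1c term nor the randomisation strata are named.

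**What is held.** Under HbA1c at 6 months, a baseline "mean HbA1c percentage will be extracted for each participating diabetes centre from routine ANDA data collection in 2021". Taking part in the 2021 audit is an inclusion criterion for centres, so every enrolled centre should have this value. Follow-up comes from the 2022 audit.

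**Loss of centres.** The sample-size section inflates 35 to 39 centres per arm for 10% non-response. Section {18b} says that if a site withdraws, its clinical outcome data "will still be collected for this trial as part of the routine ANDA data collection that the sites have agreed to participate in".

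**The concern.** Under the stated model, an enrolled centre with no 2022 data drops out of the HbA1c comparison. The 10% inflation replaces lost numbers; it does nothing about which centres are lost. Section {18b} covers a centre that leaves the trial but stays in the audit. It does not cover a centre that skips the 2022 audit. That is possible in this setting, since the protocol reports that "participation in ANDA 2021 has been impacted by the effects of COVID-19 on clinical practice", although that remark is about 2021 and recruitment.

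If the centres that fail to return differ between arms in their HbA1c level, the first co-primary estimate shifts. The second co-primary is tested only when the first is significant, so a false positive on HbA1c would also open the acceptability test. The 2021 centre mean is the natural protection and is left out of the stated model.

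The survey is exposed separately. It is an emailed link to site contacts who by then know their allocation, and no check for non-response is stated.

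**Working it through.** **1. The plan's own figure.** Inputs from Sample size {14}: difference 0.5, SD 2.3, ICC 0.070, CV of cluster size 0.730, 35 centres per arm, 3500 patients, so m = 3500/70 = 50.

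- Equal clusters: design effect = 1 + 49 × 0.07 = 4.43.
- Unequal clusters: λ = 50/(50 + 0.93/0.07) = 0.790; relative efficiency = 1 − 0.73² × 0.790 × 0.210 = 0.912; design effect = 4.43/0.912 = 4.86.
- SE = 2.3 × √(4.86 × 2/1750) = 0.171; power = Φ(0.5/0.171 − 1.96) = 83% (82% by t on 68 df).
- 35/0.9 = 38.9, so 39 per arm and 78 in total.

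The stated power of at least 80% and the 78 centres reproduce under this mixed-model form. A cruder design effect, 1 + ((1 + CV²)m − 1) × ICC = 6.295, would give 73%. The size of the trial is not the issue here.

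**2. Bias from differential centre loss.** If a fraction p of an arm's centres is lost and they lie g above those retained, the arm mean is R + p·g, where R is the retained mean. Complete cases therefore understate the arm mean by p·g. With the same g in both arms, the bias in the difference is −(excess loss) × g. Between-centre SD = 2.3 × √0.070 = 0.61. With g = 0.61 (assumed):

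| Excess loss in one arm (assumed) | Bias, HbA1c points | Share of 0.5 |
|---|---|---|
| 5% | 0.03 | 6% |
| 10% | 0.06 | 12% |
| 20% | 0.12 | 24% |

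If overall loss equals the 10% allowance and the arms are equal in size, 20% is the largest possible excess (20% against 0%).

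**3. Effect of adding the 2021 mean.** Simulation of centre means with no true effect and 39 centres per arm. Control loses 10% at random; intervention loses about 19%, more often centres with a high 2021 mean. The 2021–2022 correlation of true centre means is assumed.

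| Correlation | Unadjusted bias | SD of estimate: unadjusted → adjusted | Type I error, unadjusted |
|---|---|---|---|
| 0.5 | −0.056 | 0.167 → 0.156 | about 6% |
| 0.8 | −0.094 | 0.166 → 0.134 | about 9% |
| 0.95 | −0.112 | 0.163 → 0.114 | about 10% |

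With the 2021 centre mean as a covariate, still on complete cases, bias is about 0.00 and type I error about 5%.

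**4. Loss driven by the 2022 level instead.** With 35 centres per arm and loss of 20% against 5% depending on the 2022 mean, unadjusted bias is about −0.12. Adjustment leaves about −0.09 at correlation 0.6 and −0.05 at 0.9. The covariate helps only in part.

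**5. Precision without any loss.** Variance of a centre mean = 0.07 × 2.3² + 0.93 × 2.3²/50 = 0.370 + 0.098 = 0.469. With equal clusters, unadjusted SE = √(2 × 0.469/35) = 0.164. The observed year-to-year correlation is 0.790ρ, where ρ is the correlation of true centre means, and the adjusted SE is 0.164 × √(1 − (0.790ρ)²). This is 0.144 at ρ = 0.6 and 0.115 at ρ = 0.9.

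**6. Survey.** If 10% to 40% of one arm does not reply, non-responders are 20 to 40 points less favourable, and the other arm is unaffected (all assumed), the bias runs from 0.10 × 20 = 2 points to 0.40 × 40 = 16 points.

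**The case against.** **Bias needs more than missing data.** Loss that is alike in both arms largely cancels in the difference. In a simulation with 10% lost per arm, more often among poor 2022 performers, complete-case bias was about 0.00. The audit is routine, both arms receive the same redesigned report and slides, and withdrawn sites still report through the audit. Nothing in the protocol shows differential loss. This stands: the bias is conditional, and its size is illustrative.

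**A SAP may supply the rest.** A missing-data sensitivity analysis is often left to the SAP, which is not shown. This also stands, so the firm point is what the protocol fixes: complete cases, and a model described without a baseline term. Those extra analyses are a secondary request.

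**Replacing the complete-case sentence is not what helps.** The gain in step 3 comes from the covariate. This is correct, and the fix follows it.

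**Stronger readings that the protocol does not support:**
- *No sensitivity analysis is planned.* A per-protocol one is; what is unstated is one for missing data.
- *2021 data exist for every randomised centre, so all can be modelled jointly over both years.* The protocol says "We based the randomisation on 2019 ANDA participation and randomised prior to the formative qualitative work". A centre randomised from the 2019 list that skipped the 2021 audit has no 2021 value. Only enrolled centres must have one.
- *The 2021 data also repair the survey.* No 2021 baseline of the trial survey is described.
- *Patient-level imputation from 2021 is available.* The baseline is described as a centre mean, and no patient linkage between audits is stated.
- *The intention-to-treat label is misused.* Section {20c} uses it to mean that non-adherent sites stay in their assigned arm; it claims no protection against missing data.

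**Conclusion.** The point holds as a limited one. The protocol fixes complete cases, names no missing-data sensitivity analysis, and describes an HbA1c model that leaves the 2021 centre mean unused.

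The precision loss does not depend on any missingness: for an assumed correlation of true centre means of 0.6 to 0.9, the SE could fall from about 0.164 to between 0.144 and 0.115. The exposure to bias is conditional. It is about 0.03 to 0.12 HbA1c points (6% to 24% of the target difference) if one arm loses 5% to 20% more centres and those centres differ from the retained ones by one between-centre SD. It is near zero if loss is alike in both arms.

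A reader might infer that both co-primary results will be biased. The protocol does not support that: it gives no arm-specific rate of centre return, HbA1c recording or survey reply.

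**What to change.** **Main change.** In the primary HbA1c model, add as fixed covariates the centre's 2021 mean HbA1c, centre type (primary/secondary against tertiary/Centre of Excellence) and location (metropolitan against rural). Fit it to all enrolled centres with 2022 data. The 2021 audit window (May to July) closed before the intervention resources were released, about three months ahead of the December 2021 feedback, so the covariate precedes the intervention.

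**Small addition.** Confine the no-imputation sentence to the primary analysis. Then add:
- a shift analysis in which enrolled centres missing in 2022 take a value predicted from their 2021 mean plus a shift, varied separately by arm (for example 0 to 0.61), reporting where the conclusion changes;
- best/worst-case bounds for survey non-responders, because the 2021 data cannot help there.

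**Cost.** Wording and a little extra analysis, with no new data collection. The covariate does not remove bias from loss that depends on the 2022 level, which is why the shift analysis is worth having.
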